### Interim analyses {21b}

Statistical analysis will be done only after the trial. The trial will be stopped if individual participants report serious adverse effects during the intervention, significant deterioration in mental state or physical condition. The decision will be made by the principal investigator.

### Methods for additional analyses (e.g. subgroup analyses) {20b}

Post hoc analyses will also be performed with Bonferroni corrected t-tests to investigate the improvements in all outcome variables in pairwise comparisons across various assessment time points. Statistical significance will be set at a *p* value < 0.05. Intention-to-treat last-observation carried-forward scores will be used for the analyses. All computations will be performed using SPSS for Windows, version 22.0.

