**Methods:**

Fifty-eight patients with LLD will be recruited and randomly assigned to the active HD-tDCS or sham HD-tDCS group. In both groups, patients will receive the active or sham intervention in addition to their pre-existing antidepressant therapy, for 2 weeks with 5 sessions per week, each lasting 30 min. The primary outcome measures will be the change of depressive symptoms, clinical response and the remission rate as measured with the Hamilton Depression Rating scale (HAMD-17) before and after the intervention, and at the 4th and 12th week after the completed intervention. Secondary outcome measures include cognitive symptoms, anxiety symptoms, daily functioning and adverse effects.

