#### High–definition transcranial direct current stimulation (HD-tDCS) group

The HD-tDCS will be administered by Starstim (Neuroelectrics). All participants will receive the treatment by using the same model of the device. The HD-tDCS device can be portable and controlled wirelessly via computer software developed by the manufacturer. The montages will be a ‘4 × 1 ring set-up’, which is the most commonly used HD-tDCS setting. The centre anode electrode is surrounded by four return cathode electrodes. The anode will be placed over the left DLPFC, which is located at F3 based on the 10/20 electroencephalogram system. The four cathodal electrodes will be placed at FC1, AF3, F7 and FC5 (Additional file 1). Conductive electrode gel will be applied on the scalp at all designated electrode stimulation areas. A cap appropriate for each participants’ head size will be used to ensure that the electrodes are secured in place. Impedance checks will be performed using the Starstim software before each treatment session. A 2-mA stimulation will be delivered for 20 min, with the current gradually increased and decreased over 30 s. The patients will be instructed to relax and remain motionless during the intervention. The administrator will closely monitor the impedance throughout each session and record any side effects experienced by the participants. The participants will be allowed 5 min of rest after the intervention and will be actively asked about any discomfort. Each session will last around 30 min, with a total of 10 sessions (two consecutive weeks of treatment for 5 days per week).

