##### Primary outcome

The primary outcome will be the change of depressive symptoms, the clinical response rate and the remission rate as measured with the HAMD-17 at 12 weeks after the completed intervention. HAMD-17 is a widely used and reliable measure of depressive symptoms [21]. Scores range from 0 to 52, with higher scores indicating more severe depression. A clinical response will be defined as a reduction of 50% or more in the HAM-D-17 score in old age adult patients. A HAMD-17 score of 7 or less will be used as an indicator of remission [20].

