### Sample size {14}

The sample size was estimated using G*Power 3.1, based on the results of a tDCS meta-analysis of adult subjects by Kalu et al. [27]. In this study, active tDCS was found to be more effective than sham tDCS for the reduction of depression severity (Hedges’ g = 0.743). For 80% power and an alpha level of 5%, 48 patients (24 in each group) will be needed to detect group differences. To allow for a 20% drop-out rate, 58 patients (29 in each arm) will be recruited.

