## Data collection and management

### Plans for assessment and collection of outcomes {18a}

A trained clinician investigator who is not involved in the intervention or randomization procedure will perform the assessments. The primary and secondary outcomes will be assessed at baseline, immediately after the intervention, and 4 and 12 weeks after the intervention.

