## Statistical methods

### Statistical methods for primary and secondary outcomes {20a}

The primary outcome measurement is HAMD-17. The effect power of intervention is measured by the change of HAMD-17. If the results showed a significant improvement in the HAMD-17 measurement, it represents the intervention is effective. Both clinical response rate and remission rate are also depending on the measurement of HADM-17. They are used as an indication for the real clinical impact of the intervention. A clinical response will be defined as a reduction of 50% or more in the HAM-D-17 score. A HAMD-17 score of 7 or less will be used as an indicator of remission. Therefore, a significant result in the area of either clinical response or remission rate will indicate the clinical impact of the intervention.

To examine the presence of any group differences in demographics and clinical profile between the treatment and the sham groups at baseline, chi-squared tests and *t*-tests will be performed for categorical and continuous variables respectively.

Two-way repeated measures analysis of variance (ANOVA) will be used to examine the effect of time and treatment conditions on the HAM-D-17 scores and other cognitive and IADL measurements across various assessment time points. The analysis would be adjusted to age, sex, medication type/dose, relapse episodes and other potential confounders. If both depressive symptoms and cognitive function improved, mediation analysis will be done to determine the cognitive function improvement is mediated by the improvement of depressive symptoms or vice versa.

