## Discussion

This is the first RCT that evaluates the effectiveness and tolerability of HD-tDCS in older adults with depression. Most studies tend to assess effectiveness in the adult population and only a few studies have evaluated the effects of tDCS on cognitive function in depression.

This randomized controlled trial aims to evaluate the effectiveness of HD-tDCS as augmentation therapy with antidepressants in ameliorating depressive symptoms in patients with LLD who had a suboptimal response to treatment. To this aim, the trial compares the effect of HD-tDCS and sham-control HD-tDCS on improving depressive symptoms in addition to the pre-existing antidepressant regimen. The depressive symptoms are operationalized into three levels, namely the change of depressive symptoms, the clinical response and the remission rate measured by HAMD-17. Secondary objectives are to examine the intervention impact on the cognitive function, anxiety symptoms, daily functioning and adverse effects at the end of the intervention. We also plan to detect any sustained effect by checking the changes at the 4th week and 12th week after the finished intervention.

The results from this trial will be useful for the management of patients with LLD because a new safe treatment option is needed to alleviate depressive symptoms for those showing suboptimal responses to conventional antidepressants. It is also expected that HD-tDCS is effective in improving cognitive function which is often significantly impaired in LLD. Based on its effect on neural plasticity and enhancement of serotonin and cognitive function, our study aims at confirming the efficacy of HD-tDCS as augmentation therapy for antidepressants in patients with LLD.

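### Last observation carried forward lets an earlier HAMD-17 score stand in for the 12-week primary value, with a bias whose direction cannot be known in advance

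*Protocol article*

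**What the plan says.** The missing-data rule is one sentence at the end of the protocol article's section on additional analyses {20b}: "Intention-to-treat last-observation carried-forward scores will be used for the analyses". It follows the post hoc tests and stands beside the general statements on significance level and software. Section {20c}, whose title covers missing data, deals only with missed treatment sessions and a comparison of compliant with non-compliant participants. No other missing-data method is named.

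The Primary outcome section defines change, response and remission "as measured with the HAMD-17 at 12 weeks after the completed intervention". Section {18a} has outcomes "assessed at baseline, immediately after the intervention, and 4 and 12 weeks after the intervention", so the scores available to carry are baseline, end of treatment and week 4. Treatment itself is ten sessions over two weeks. The Sample size section plans for loss: "To allow for a 20% drop-out rate, 58 patients (29 in each arm) will be recruited". The Discussion gives the purpose of the later visits: "We also plan to detect any sustained effect by checking the changes at the 4th week and 12th week after the finished intervention". The planned model in {20a} is: "Two-way repeated measures analysis of variance (ANOVA) will be used to examine the effect of time and treatment conditions on the HAM-D-17 scores".

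**The concern.** Carrying a score forward assumes that the patient would have stayed exactly where last seen. In this design that covers up to 12 weeks without stimulation, over which the plan wants to learn whether any benefit lasts. Depending on when a patient leaves, the substituted week-12 value is one of three:

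- **Lost during treatment:** baseline is carried. The patient counts as unchanged and a non-responder and, because entry requires a HAMD-17 of at least 8, as not remitted.
- **Lost between end of treatment and week 4:** the end-of-treatment score is carried, possibly the best score the patient would have had.
- **Lost between week 4 and week 12:** the week-4 score is carried.

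Each is then analysed as a measured value, so the uncertainty about it is ignored. At stake are the week-12 treatment difference, its error rate, and any statement that the effect is or is not sustained.

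**Working it through.** **Inputs from the protocol.** Drop-out 20%; 29 per arm; Hedges' g = 0.743; visits at baseline, end of treatment, week 4 and week 12. The recruitment figure reproduces as 48 × 1.2 = 57.6, rounded to 58. At 20%, about 0.20 × 29 = 5.8, or 6 patients per arm, would have a substituted week-12 value.

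**Assumptions, because the protocol does not give them.** The 0.743 SD applies at end of treatment; drop-out is equal in both arms and unrelated to outcome; its timing is varied; the course after treatment is varied.

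**Formula.** Let d be the drop-out share, p_k the share of drop-outs last seen at visit k (baseline, end of treatment, week 4), and δ_k the true arm difference at that visit (zero at baseline). The week-12 difference under carry-forward is

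(1 − d) × δ_week12 + d × Σ p_k δ_k.

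**Effect vanishes: differences 0.743, 0.3715 and 0 at the three post-baseline visits.** The true week-12 difference is 0.

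| Last score carried | Calculation | Spurious difference (SD) | Simulated rejection |
|---|---|---|---|
| All end of treatment | 0.20 × 0.743 | 0.149 | about 10% |
| Half end of treatment, half baseline | 0.20 × 0.5 × 0.743 | 0.074 | 6.1% |
| Spread evenly over three intervals | 0.20 × (0 + 0.743 + 0.3715)/3 | 0.074 | about 6% |
| All baseline | 0.20 × 0 | 0 | 5.3% |

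The rejection rates come from 6,000 simulated trials per case, 29 per arm, with a nominal two-sided 5% test at week 12 and a between-visit correlation of 0.5 or 0.6. Across these settings the first row ranged from 9.2% to 10.4% and the third from 6.0% to 6.3%. Monte Carlo error at a true 5% is √(0.05 × 0.95/6000) = 0.3 percentage points. Observed week-12 data alone, in the first-row scenario, gave a difference of 0.00 SD and 5.5% rejection.

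With all drop-outs carrying the end-of-treatment score, other drop-out rates give 0.10 × 0.743 = 0.074 SD and 0.30 × 0.743 = 0.223 SD.

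**Half the effect remains: 0.743, 0.55, 0.37.** Even spread: 0.80 × 0.37 + 0.20 × (0 + 0.743 + 0.55)/3 = 0.296 + 0.086 = 0.382, against a true 0.37. The bias is negligible.

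**Effect fully sustained: 0.743 throughout.**

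- Even spread: 0.80 × 0.743 + 0.20 × (2/3) × 0.743 = 0.594 + 0.099 = 0.693 SD.
- All carrying baseline: 0.80 × 0.743 = 0.594 SD (simulated 0.596). Simulated power is 71.0%, against 79.0% from observed week-12 data.
- All carrying end of treatment: 0.743, no bias.

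With equal drop-out throughout, the bias is positive, near zero or negative according to timing and time course.

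**The case against.** **The sentence stands under additional analyses.** It may have been meant for the post hoc tests only. But its wording is unrestricted and no other method is given for the primary analysis, so the natural reading is that it applies throughout.

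**A separate analysis plan may exist.** It could add sensitivity analyses. The point, however, is a method the protocol has chosen, not one it has left out.

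**The primary time point is not uniform.** The abstract lists assessments "before and after the intervention, and at the 4th and 12th week after the completed intervention", whereas the Outcomes section fixes week 12. Week 12 is in both, and week-4 scores would be carried into as well, so the problem remains.

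**A reader might infer that carry-forward will make a transient effect look sustained, with error rates of 10% or more.** The documents do not support that. It needs the effect to be gone by week 12 and all loss to fall between end of treatment and week 4. Drop-out timing is not stated, and the pilot (open-label, 15 patients) reported benefit lasting to 1 and 3 months. If the effect lasts, carry-forward is conservative or neutral in the cases above.

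**A reader might also infer that unequal drop-out between arms is what drives the bias.** In the vanishing-effect case with end-of-treatment scores carried and a flat sham course after treatment, 30% active with 10% sham gives about 0.22 SD and 15% rejection. So does 30% in both arms: 0.30 × 0.743 = 0.223. The excess comes from the 30% loss in the active arm, which is above the planned 20%, and not from the imbalance.

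**The comparison favours observed-data analysis.** This stands: drop-out was simulated as unrelated to outcome, so that analysis is unbiased by construction. The simulations also test a week-12 contrast. They do not describe the group-by-time test of the planned ANOVA, whose interaction is truly non-zero when an effect fades.

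**Conclusion.** The point holds as a should-fix. Carry-forward builds an unsupported assumption of no further change into the outcome meant to test durability, for up to about one in five patients at the planned drop-out.

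If the effect vanishes by week 12, the false week-12 difference is about 0.07 SD with even timing and at most 0.15 SD at 20% drop-out, with rejection of about 6% to 10% against 5%. If the effect is sustained, 0.743 SD becomes about 0.69 SD with even timing and about 0.60 SD if all drop-outs carry baseline. These figures rest on the assumed time courses, on equal drop-out unrelated to outcome, and on applying the meta-analytic 0.743 at end of treatment. Response and remission are affected by the same mechanism; no size is given for them here. What does not depend on these assumptions is that a substituted value is treated as measured, with a bias whose sign cannot be known in advance.

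**What to change.** Replace the carry-forward sentence in {20b} and, for HAMD-17, the repeated-measures ANOVA in {20a}, with wording such as:

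> The primary analysis of HAMD-17 is a likelihood-based mixed model for repeated measures on all observed scores of all randomised patients, with arm, visit, arm-by-visit interaction and baseline HAMD-17 and an unstructured covariance matrix. The primary comparison is the arm difference at week 12. Response and remission at week 12 are analysed after multiple imputation consistent with this model.

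Keep carry-forward at most as a sensitivity analysis. Set beside it an analysis in which drop-outs are assumed to do worse than the model predicts. This second analysis is needed because the mixed model is unbiased only if drop-out depends on observed data.

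The cost is revised wording in two sections, a little programming, and somewhat wider week-12 intervals, which reflect the missing information. No new data or patients are needed. Section {21b} places all statistical analysis after the trial, so the change can be made before any analysis is run.

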### Methods in analysis to handle protocol non-adherence and any statistical methods to handle missing data {20c}

Participants will be allowed 2 non-consecutive missed visits and extra sessions will be performed to complete the total 10 sessions. Participants with more than 2 non-consecutive missed visits will be defined as non-compliance subjects. Further analysis would be done to compare the difference between compliance and non-compliance subjects.

### Plans to give access to the full protocol, participant-level data and statistical code {31c}

Protocol could be assessed by the public through the clinical trial register website. The study results will be published in an international journal. There are no plans to release the participant-level data.

## Oversight and monitoring

### Composition of the coordinating centre and trial steering committee {5d}

The principal investigator and other co-investigators, who are psychiatrists and neuroscientists, will be responsible to oversight and monitor the whole trial. Specialist psychiatrists in hospitals under Hospital Authority are responsible for the diagnosis of patients’ psychiatric disorders, recruiting patients and signing consents. If there are any disputes or logistic problems, the final decision will be made by the principal investigator.

### Composition of the data monitoring committee, its role and reporting structure {21a}

Data monitoring will be carried out by an independent data monitoring committee, which is composed of the research psychiatrist, a methodologist, a statistician and a data manager. The committee will ensure that all the data collection, storage and management procedures are carried out in accordance with the research protocol and the regulations. Committee members will keep track of and verify the data collection process. In case of any technical or procedural problems or uncertainties, the committee members are responsible for reporting to the principal investigator.

### Adverse event reporting and harms {22}

A checklist of potential adverse effects associated with t-DCS administration will be generated with reference to the available literature. During the stage of obtaining informed consent from the participants, all potential adverse effects associated with the use of t-DCS will be clearly listed and explained to the participants. In case there is any adverse effect, it will be immediately recorded in the clinical management system (CMS) and the data record form and the patient involved will be monitored by the principal investigator until resolution or stabilization. The patient condition will be closely monitored and the degree of seriousness of the adverse effect will be evaluated by the principal investigator who will then contact the trial promotor for further coordination.]

### Frequency and plans for auditing trial conduct {23}

N/A. The monitoring of the progress and quality of the trial will be conducted every month.

### Plans for communicating important protocol amendments to relevant parties (e.g. trial participants, ethical committees) {25}

Any amendments in the protocol will be discussed among all investigators and reported to the ethic committees responsible for the trial approval.

### Dissemination plans {31a}

Participants will receive a summary of their assessment reports after they finished the trial. The study result will be published in an international journal and presented in a relevant conference.

## Discussion

This is the first RCT that evaluates the effectiveness and tolerability of HD-tDCS in older adults with depression. Most studies tend to assess effectiveness in the adult population and only a few studies have evaluated the effects of tDCS on cognitive function in depression.

This randomized controlled trial aims to evaluate the effectiveness of HD-tDCS as augmentation therapy with antidepressants in ameliorating depressive symptoms in patients with LLD who had a suboptimal response to treatment. To this aim, the trial compares the effect of HD-tDCS and sham-control HD-tDCS on improving depressive symptoms in addition to the pre-existing antidepressant regimen. The depressive symptoms are operationalized into three levels, namely the change of depressive symptoms, the clinical response and the remission rate measured by HAMD-17. Secondary objectives are to examine the intervention impact on the cognitive function, anxiety symptoms, daily functioning and adverse effects at the end of the intervention. We also plan to detect any sustained effect by checking the changes at the 4th week and 12th week after the finished intervention.

The results from this trial will be useful for the management of patients with LLD because a new safe treatment option is needed to alleviate depressive symptoms for those showing suboptimal responses to conventional antidepressants. It is also expected that HD-tDCS is effective in improving cognitive function which is often significantly impaired in LLD. Based on its effect on neural plasticity and enhancement of serotonin and cognitive function, our study aims at confirming the efficacy of HD-tDCS as augmentation therapy for antidepressants in patients with LLD.

One of the limitations of the trial is the measurement of cognitive function by various tests e.g. HK-MoCA in which practice effects might come into play when evaluating the improvements in verbal fluency and overall cognitive ability. Although the same dosage and timing of antidepressants will be kept the same for at least 4 weeks prior to the study, the possibility of the effect from a change of medications cannot be excluded, which may lead to an overestimation of the effect by tDCS. Furthermore, the diversities of the clinical profiles might be potential confounding factors, including the types of antidepressants being used, the degree of suboptimal treatment response and treatment resistance, or the duration of the depressive symptoms. Subgroup analysis will be performed to eliminate the bias from confounding factors and enhance the validity of the trial.

## Trial status

Protocol version: 23 February 2022, Version n˚1.

Date of recruitment: 1st Sep 2020.

End of recruitment: estimated to be Jan 2023.

## Data Availability

Data will be available upon request to the investigator.

## Abbreviations

a-HD-tDCS: Active high-definition transcranial direct current stimulation
DLPFC: Dorsolateral prefrontal cortex
DSM-5: Diagnostic and Statistical Manual of Mental Disorders (DSM-5)
HAMA: Hamilton Anxiety Rating Scale
HAMD: Hamilton Depression Rating Scale
HD-tDCS: High-definition transcranial direct current stimulation
HK-MoCA: Hong Kong Chinese version of the Montreal Cognitive Assessment
IADL-CV: Hong Kong Chinese version of the Lawton Instrumental Activities of Daily Living Scale
LLD: Late-life depression
RCTs: Randomized controlled trials
s-HD-tDCS: Sham high-definition transcranial direct current stimulation
tDCS: Transcranial direct current stimulation
